### 3.1. Measurement Instruments

To identify DIVA patients during PIVC catheterization, two scales will be used depending on the patient’s age:

For patients aged ≥14 years, the A-DICAVE scale [11] will be applied. This scale consists of three items: vein visualization (scored 0–2), vein palpation (scored 0–2), and a history of puncture difficulty (scored 0–1). The total score is categorized as follows: easy (0–2 points) and difficult (3–5 points).

For patients aged <14 years, the DIVA4 scale [2] will be used. This scale, scored 0–10, includes four items: visible vein after tourniquet application (0–2 points), palpable vein after tourniquet application (0–2 points), age (≥3 years: 0 points; 1–2 years: 1 point; <1 year: 3 points), and history of prematurity with gestational age < 38 weeks (0–3 points). It has been demonstrated that scores > 4 typically indicate the need for multiple punctures to achieve adequate venous access.

In order to assess the level of satisfaction of professionals, patients and their families, an ad hoc instrument will be used, based on a 5-point Likert scale, ranging from 1 = “not at all satisfied” to 5 = “very satisfied”. Each item will be rated with a value from 1 to 5. To determine the general level of satisfaction, the following ranges of interpretation have been established:Not at all satisfied.Not very satisfied.Satisfied.Quite satisfied.Very satisfied.

To assess the satisfaction levels of professionals, patients, and their families, a 5-point Likert satisfaction scale will be applied. If patients are unable to express their satisfaction, only the response from their family members will be recorded.

Pain assessment will utilize numerical scales (0–10):○For adults and children aged > 7 years, the Visual Analogue Scale (VAS) [30] will be used.○For children aged < 5 years, the FLACC scale (Face, Legs, Activity, Cry, Consolability) [31] will be applied.○For adults with cognitive impairments, the PAINAD scale (Pain Assessment in Advanced Dementia) [32] will be employed.

Once the corresponding technique has been carried out, the data from the measuring instruments will be recorded through the form that will have the necessary items for their evaluation, together with the rest of the variables, as shown in Table 2.

### 3.2. Data Collection System

The collaborators will be provided with the necessary training for data collecting. To ensure the quality of care and patient safety with respect to the techniques to be developed in the study, the collaborators must be nurses from the service who have received specific training in ultrasound-guided puncture and have a minimum experience in the service of 2 years, thus being considered competent nurses according to Patricia Benner’s model [33].

Collaborators will be provided with a data collection form accessible from the point of care. A separate form will be used for each technique (PIVC or ABG), ensuring that the data are transferred to a dedicated database specifically prepared for the study. The database will record all relevant variables (Table 2).

The study will be coordinated by the principal investigator, attached to the ED of the hospital, who will be responsible for compliance with the protocol, data integrity, and the supervision of the research team.

The governance of the project will be overseen by an Internal Control Committee, composed of members of the emergency department, which will meet quarterly to review study progress, ethical compliance, and adverse events.

The involvement of an external monitoring committee is not foreseen, given the low-risk nature of the study.

All adverse events shall be documented in a specific data collection form (CRF), with details on their nature, severity, duration, treatment required and outcome.

Adverse events will be considered any unanticipated clinical incident temporally related to the venous or arterial puncture procedure, such as: extensive hematoma, local infection, phlebitis, persistent pain, or vascular damage. These events shall be recorded by the investigator immediately after the procedure and during the clinical follow-up of the patient in the emergency department. An intermediate safety analysis will be carried out when 50% of the planned recruitment is reached.

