**Figure 3 nursrep-15-00177-f003:**
[figure not shown]
Ultrasound canalization PIVC. *Transversal Plane. (Own source)*.

**Table 1 nursrep-15-00177-t001:** Steps of the EG ultrasound-guided technique.

Steps of the EG Ultrasound-Guided Technique	
**STEP 1**	Patient identification and procedure explanation.
**STEP 2**	Preparation of necessary materials.
**STEP 3**	Ultrasound-guided examination of the limb to be punctured (RaPeVa): Identification of vessel patency. Identification of nearby structures to prevent injury during puncture.
**STEP 4**	Selection of an appropriate vessel (depth, diameter, and patency): PIVC: Vessel at a depth of <5 mm, with a diameter at least two-thirds larger than the catheter. Avoid areas of joints or bony prominences. ABG: Depth appropriate for the needle used.
**STEP 5**	Preparation of the puncture site: Hand hygiene. Skin disinfection with 2% alcoholic chlorhexidine (2% aqueous chlorhexidine for patients under 2 years old). Non-touch technique.
**STEP 6**	Ultrasound-guided puncture: Appropriate angle based on vessel depth and puncture system. PIVC: Verification of catheter tip placement using ultrasound imaging. ABG: Visualization of the needle inside the artery.
**STEP 7**	PIVC: Verification of catheter patency, placement of an extension system, and catheter fixation with a transparent, semi-permeable dressing. ABG: Arterial blood sample collection, followed by application of pressure at the puncture site for 5 min (10 min for anticoagulated patients).

**Table 2 nursrep-15-00177-t002:** RTC variables. Source: produced by the authors.

RTC Variables	
**Dependent Variables**	**Description**
Type of technique	Arterial puncture, peripheral venous cannulation with short PIVC
Total score on the A-DICAVE scale	From 0 to 10 score in patients below 14
Score in DIVA scale	From 0 to 8 score in patients over 14
Score of every item on the A-DICAVE scale	Score of every item on the scale
Success	Successful result (Yes/No)
Number of attempts	Number of punctures attempts to achieve cannulation
Numbers of nurses attempting	Number of nurses to achieve cannulation
Time taken in the technique	Time in minutes taken for the procedure
Cannulation zone	Pace of insertion of the catheter (hand, forearm, flexure, arm)
Catheter gauge	Measurement in gauges of the used catheter
Pain	EAV scales (oriented patient), FLACC (pediatric patient) or PAINAD (disorientated patient)
Permanence of the vascular access	Permanence time of the catheter

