Secondary effects	Type of effects (extravasation, phlebitis, obstruction, others)
Patient satisfaction	Level of satisfaction (5-point Likert scale)
Family satisfaction	Level of satisfaction of the family (5-point Likert scale)
Professional satisfaction	Level of satisfaction of the professional who applied the technique (5-point Likert scale)
**Independent variables**	**Description**
Age	Years
Gender	Male, female, nonbinary
Reason for the consultation	Reason for the assistance according to nursing record
Emergency zone	Assigned emergency zone
Triage level	Classification SET (I, II, III, IV, V)
Predisposing factors of DIVA	Factors such as addiction, obesity, old age among others
**Procedure variables**	**Description**
Type of technique	Traditional, ultrasound guided
Transducer placement	Longitudinal, transversal, none
**Confusion variables**	**Description**
Medication given	Medication used through the access
Dilution volume	Volume in ml of the medication dilution
Time of administration	Taken time in minutes of the administration
Conscience level	Glasgow scale
Agitation	Yes/No

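### Adverse events are recorded only up to the end of the ED stay, although catheter dwell time is collected, and the word *unanticipated* contradicts the listed events

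*Protocol article*

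**What the plan says.** Section 3.2 (Data Collection System) defines an adverse event as "any unanticipated clinical incident temporally related to the venous or arterial puncture procedure" and gives examples: "such as: extensive hematoma, local infection, phlebitis, persistent pain, or vascular damage". The investigator is to record these right after the procedure and "during the clinical follow-up of the patient in the emergency department". The section names no later time point. An internal committee of ED members reviews adverse events, and a safety analysis is planned at half of recruitment.

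Table 2 holds two further items that bear on this. *Permanence of the vascular access* is described as "Permanence time of the catheter". *Secondary effects* is described as "Type of effects (extravasation, phlebitis, obstruction, others". Both are listed as dependent variables, and neither has a stated observation window. Section 3.2 says that the study database will hold the Table 2 variables.

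On timing, Section 3.1 says: "Once the corresponding technique has been carried out, the data from the measuring instruments will be recorded through the form", together with the other variables in Table 2.

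**The concern.** The recording window is tied to the place of care and not to the period at risk. A peripheral catheter can stay in when the patient moves to a ward. Local infection, phlebitis and persistent pain can begin or continue after that move. For the same catheter, the plan wants the dwell time but stops adverse event recording when the ED stay ends.

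Two things are at stake. First, a difference between arms in later complications, in either direction, could go unseen on the adverse event form and in the 50% safety analysis. The Conclusions (Section 5) nevertheless give better safety as a reason to adopt ultrasound if it proves effective. Second, the length of the window may depend on the treatment. The Discussion expects fewer attempts to contribute to shorter ED stays. If so, the ultrasound arm would be watched for less time and would show fewer late events for that reason alone.

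The definition adds a smaller problem. Every example given for an *unanticipated* incident is a known complication of puncture. The recorder therefore has no clear rule for known complications that the sentence does not name.

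**Working it through.** The plan states no figure here to reproduce: no ED length of stay, no time to onset, no complication rate. The check is mainly a comparison of the stated rules.

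**Rules side by side**

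| Item | Where | Window stated | Events |
|---|---|---|---|
| Adverse events | 3.2 | After the procedure and during the ED stay | Extensive hematoma, local infection, phlebitis, persistent pain, vascular damage (as examples) |
| Secondary effects | Table 2 | None | Extravasation, phlebitis, obstruction, others |
| Permanence of the vascular access | Table 2 | None, but a dwell time implies observation to removal | Not applicable |
| Form completion | 3.1 | After the technique | All Table 2 variables |

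Three things follow.

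1. Phlebitis is in both event lists, with an ED limit in one and no window in the other.
2. Dwell time cannot be known when the technique has just been completed. Some later data collection must therefore be intended, but the article names neither the source nor the collector.
3. The adverse event rule is the only one with an explicit end, and that end comes before removal for any patient who leaves the ED with the catheter in place.

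**How much could be missed (assumed inputs only)**

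Let T be the ED observation time after insertion and m the median time to onset of a delayed event, with exponential onset. The share captured is 1 − 2^(−T/m). For example, T = 6 h and m = 24 h gives 1 − 2^(−0.25) = 15.9%.

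| T (assumed) | m = 12 h | m = 24 h | m = 48 h | m = 72 h |
|---|---|---|---|---|
| 2 h | 10.9% | 5.6% | 2.8% | 1.9% |
| 4 h | 20.6% | 10.9% | 5.6% | 3.8% |
| 6 h | 29.3% | 15.9% | 8.3% | 5.6% |
| 12 h | 50.0% | 29.3% | 15.9% | 10.9% |
| 24 h | 75.0% | 50.0% | 29.3% | 20.6% |

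The range is 2% to 75%. In this model more than half of the delayed events are missed only when the ED stay is shorter than the median onset.

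**Unequal windows (assumed inputs only)**

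Suppose the true late-event rates are equal, the control arm stays 6 h and the ultrasound arm 4 h. With m = 24 h the captured shares are 15.9% and 10.9%, a ratio of 10.9 / 15.9 = 0.69. With m = 12 h the ratio is 20.6 / 29.3 = 0.70. Recorded late events would then be about 30% fewer in the ultrasound arm with no true difference. The two-hour gap is an illustration; the documents give no size for the expected shortening.

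**The case against.** The strongest reply is that adverse events and secondary effects are two separate data items. The ED limit governs only the first. Obstruction and extravasation appear only in the second, which has no ED limit, is not restricted to unanticipated events and has an open category for others. An article also commonly leaves collection windows for single variables to the full protocol or the case report form. This stands in part. A reader might infer that every complication is recorded only in the ED, and the documents do not say so. For secondary effects the window is unstated, which is different from ED-only. The adverse event window, however, is stated in the article, so it was not left to another document.

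A reader might also infer that most late complications will be missed. That rests wholly on assumed stay and onset times, and the grid above includes values of one half and more. Hematoma and vascular damage are likely to show at or soon after puncture, and the calculation does not apply to them.

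Nor does *unanticipated* exclude phlebitis or infection, since the same sentence names them as adverse events. It is a contradiction in wording, and no loss of data has been shown from it.

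Finally, the dwell-time argument does not reach the arterial part (80 of 114 + 80 = 194 planned participants), where no catheter remains, nor catheters removed before the patient leaves the ED. No confirmatory safety comparison is specified, and the sample sizes rest on number of attempts and first-attempt success. All of this limits the point but does not remove it.

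**Conclusion.** The point holds in a limited form. As written, the adverse event form stops at the end of the ED stay although some listed events can occur or persist later, and although the plan collects catheter dwell time. The form and the 50% safety analysis may therefore miss events after the ED. The window could be shorter in the ultrasound arm if the Discussion's expectation about ED stays is right. The share missed and any bias between arms cannot be sized from the documents.

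The conclusion rests on two premises: that some patients leave the ED with the catheter in place, and that infection, phlebitis or pain can arise or persist after that. The efficacy comparison is not affected. This is an inexpensive improvement to safety ascertainment and does not invalidate the design.

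**What to change.** - **Peripheral catheters:** record adverse events and secondary effects from insertion to catheter removal, by the same rule in both arms, collected when the removal time is obtained for *Permanence of the vascular access*. Name the source and the person who collects the data after the ED.
- **Arterial puncture:** state one observation window, equal in both arms and not dependent on length of ED stay.
- **Definition:** delete *unanticipated*, so that any clinical incident temporally related to the puncture counts.
- **Event lists:** reconcile Section 3.2 with the *Secondary effects* row of Table 2, and say how the two items relate.

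The cost is a change of wording, some data entry after the patient leaves the ED, and incomplete data for patients with no later record. These gaps should be reported by arm. The added work should be small if dwell time is already traced to removal, but the documents do not state the source for dwell time, so this has to be confirmed.

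If the window is not extended, safety conclusions should be limited to events during the ED stay.

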## 4. Discussion

An extensive review of the literature was conducted to ensure this study protocol addresses current gaps in evidence, offering new insights into DIVA patient identification and the use of ultrasound-guided vascular access techniques in emergency departments (ED). This protocol integrates validated identification scales for DIVA, enhancing the reliability of patient categorization and improving clinical outcomes.

In ED settings, few studies have employed validated methods for identifying DIVA patients in conjunction with ultrasound-guided techniques from the outset. Most existing studies rely on subjective observations, such as palpable veins or the number of attempts required for successful venipuncture. Notable works, including those by Rodríguez-Herrera et al. [19] and Rubiera [34], have highlighted the potential of early identification in improving procedural success rates. The A-DICAVE scale, validated by [name] in 2020 [15,35], is among the few scales developed specifically for this purpose, yet its adoption in practice has been limited. To address this, our protocol incorporates the A-DICAVE scale to provide a standardized, objective approach for identifying DIVA patients.

Research comparing traditional and ultrasound-guided peripheral intravenous catheter (PIVC) insertion in EDs has consistently shown that ultrasound guidance improves first-attempt success and reduces the number of attempts required. Studies by Rubiera et al. [34] and Rodríguez-Herrera et al. [19] support these findings, yet these studies often lacked probabilistic sampling or failed to control for important variables like the use of medications through PIVCs. In contrast, our study accounts for such variables and includes confounding factors such as the cognitive state of patients, which may influence procedure outcomes.

Although patient satisfaction with ultrasound-guided techniques has been assessed in various studies [36], practitioner satisfaction remains underexplored. Given its impact on the adoption of new techniques in clinical practice, our protocol incorporates the evaluation of practitioner satisfaction as an additional key variable.

Evidence supporting the benefits of ultrasound-guided PIVC insertion is robust, with a meta-analysis by Tran et al. [37] demonstrating a significant improvement in first-attempt success rates. However, these studies were not conducted in ED settings, highlighting the need for research tailored to the unique demands of EDs. Our protocol aims to fill this gap by focusing on ED populations, where challenges such as high patient turnover and time constraints are prevalent.

Regarding pain assessment, while tools like the Visual Analog Scale (VAS) have been used to measure discomfort, they typically exclude pediatric patients or those with cognitive impairments. To ensure a comprehensive evaluation, our study includes alternative pain assessment scales suitable for a broader patient population, including those with cognitive challenges.

The use of ultrasound for arterial punctures in EDs remains underexplored, with most research focused on critical care or anesthesia settings [38,39]. However, studies such as that by Grandpiere et al. [3] have demonstrated that ultrasound guidance reduces the number of attempts and associated pain in difficult arterial access cases. Our study builds on this evidence, extending its focus to include patients with cognitive impairments and healthcare professional satisfaction.

The benefits of ultrasound-guided techniques extend beyond clinical outcomes, leading to a reduction in resource usage. Fewer attempts reduce material consumption and optimize staff allocation, contributing to faster procedures, shorter ED stays, and quicker test results [6,11,40,41,42]. Additionally, the increased efficiency enhances healthcare professional satisfaction and improves overall workflow in EDs.

While this study may face limitations, such as the inability to implement a double-blind design, random sampling and data coding ensure the reliability of our findings. The single-center design could also limit generalizability; however, the protocol’s methodological rigor allows for adaptation to other centers, providing flexibility for future studies.

In summary, this study addresses critical gaps in the literature by incorporating validated DIVA identification scales and ultrasound-guided techniques for PIVC and arterial access in ED settings. By considering confounding variables and focusing on a representative patient sample, our research aims to provide valuable evidence to enhance ED practices and improve patient care.

## 5. Conclusions

This study protocol will allow for the development of a study to evaluate the effectiveness of ultrasound-guided vascular access compared to traditional methods in DIVA patients identified by validated scales in the ED. After the implementation of this protocol, it is expected that ultrasound guidance will optimize ED workflows, improve patient comfort, and reduce resource consumption. If proven effective, ultrasound-guided techniques should be incorporated into standard ED protocols to improve safety, patient satisfaction, and clinical efficiency.

## Figures and Tables

**Figure 1 nursrep-15-00177-f001:**
[figure not shown]
Flow chart RTC. Produced by the authors.

**Figure 2 nursrep-15-00177-f002:**
[figure not shown]
Ultrasound image of venous access. *Longitudinal plane. (Own source)*.

**Figure 3 nursrep-15-00177-f003:**
[figure not shown]
Ultrasound canalization PIVC. *Transversal Plane. (Own source)*.

**Table 1 nursrep-15-00177-t001:** Steps of the EG ultrasound-guided technique.

Steps of the EG Ultrasound-Guided Technique	
**STEP 1**	Patient identification and procedure explanation.
**STEP 2**	Preparation of necessary materials.
**STEP 3**	Ultrasound-guided examination of the limb to be punctured (RaPeVa): Identification of vessel patency. Identification of nearby structures to prevent injury during puncture.
**STEP 4**	Selection of an appropriate vessel (depth, diameter, and patency): PIVC: Vessel at a depth of <5 mm, with a diameter at least two-thirds larger than the catheter. Avoid areas of joints or bony prominences. ABG: Depth appropriate for the needle used.
**STEP 5**	Preparation of the puncture site: Hand hygiene. Skin disinfection with 2% alcoholic chlorhexidine (2% aqueous chlorhexidine for patients under 2 years old). Non-touch technique.
**STEP 6**	Ultrasound-guided puncture: Appropriate angle based on vessel depth and puncture system. PIVC: Verification of catheter tip placement using ultrasound imaging. ABG: Visualization of the needle inside the artery.
**STEP 7**	PIVC: Verification of catheter patency, placement of an extension system, and catheter fixation with a transparent, semi-permeable dressing. ABG: Arterial blood sample collection, followed by application of pressure at the puncture site for 5 min (10 min for anticoagulated patients).

**Table 2 nursrep-15-00177-t002:** RTC variables. Source: produced by the authors.

RTC Variables	
**Dependent Variables**	**Description**
Type of technique	Arterial puncture, peripheral venous cannulation with short PIVC
Total score on the A-DICAVE scale	From 0 to 10 score in patients below 14
Score in DIVA scale	From 0 to 8 score in patients over 14
Score of every item on the A-DICAVE scale	Score of every item on the scale
Success	Successful result (Yes/No)
Number of attempts	Number of punctures attempts to achieve cannulation
Numbers of nurses attempting	Number of nurses to achieve cannulation
Time taken in the technique	Time in minutes taken for the procedure
Cannulation zone	Pace of insertion of the catheter (hand, forearm, flexure, arm)
Catheter gauge	Measurement in gauges of the used catheter
Pain	EAV scales (oriented patient), FLACC (pediatric patient) or PAINAD (disorientated patient)
Permanence of the vascular access	Permanence time of the catheter
Secondary effects	Type of effects (extravasation, phlebitis, obstruction, others)
Patient satisfaction	Level of satisfaction (5-point Likert scale)
Family satisfaction	Level of satisfaction of the family (5-point Likert scale)
Professional satisfaction	Level of satisfaction of the professional who applied the technique (5-point Likert scale)
**Independent variables**	**Description**
Age	Years
Gender	Male, female, nonbinary
Reason for the consultation	Reason for the assistance according to nursing record
Emergency zone	Assigned emergency zone
Triage level	Classification SET (I, II, III, IV, V)
Predisposing factors of DIVA	Factors such as addiction, obesity, old age among others
**Procedure variables**	**Description**
Type of technique	Traditional, ultrasound guided
Transducer placement	Longitudinal, transversal, none
**Confusion variables**	**Description**
Medication given	Medication used through the access
Dilution volume	Volume in ml of the medication dilution
Time of administration	Taken time in minutes of the administration
Conscience level	Glasgow scale
Agitation	Yes/No

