### 2.6. Statistical Methods

The data will be analyzed using SPSS software, version 22. Initially, normality tests will be performed to assess the distribution, homogeneity, and comparability of the sample, employing kurtosis, skewness coefficients, and the Shapiro–Wilk test. A descriptive analysis will then be conducted using measures of central tendency and dispersion (SD) for quantitative variables, alongside calculations of the median and interquartile range (IQR). Qualitative variables will be expressed as frequencies (n) and percentages (%).

Subsequently, appropriate statistical tests will be conducted to determine whether the hypothesis can be rejected, analyzing relationships between the different variables. For qualitative variables, the Chi-square test will be used, or Fisher’s exact test if values < 5 are observed in the sample. For quantitative variables, Student’s t-test will be applied, or the Mann–Whitney U test in cases where the data do not follow a normal distribution.

In all calculations performed in the study, an alpha error of 0.05 and a beta error of 0.2 will be considered, with a 95% confidence level.

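### By default, pain scores from three non-equivalent instruments are compared together, and the rules for assigning the instruments do not agree

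*Protocol article*

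**What the plan says.** Table 2 has a single dependent variable for pain, scored by "EAV scales (oriented patient), FLACC (pediatric patient) or PAINAD (disorientated patient" (I read EAV as the Visual Analogue Scale). Section 3.1 puts the three instruments on one range: "Pain assessment will utilize numerical scales (0–10". Its assignment rules are:

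- "For adults and children aged > 7 years, the Visual Analogue Scale (VAS"
- "For children aged < 5 years, the FLACC scale"
- "For adults with cognitive impairments, the PAINAD scale"

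Section 2.6 sets one rule for numerical outcomes: "For quantitative variables, Student’s t-test will be applied, or the Mann–Whitney U test in cases where the data do not follow a normal distribution". It names no stratum, covariate or instrument term. Section 2.5 names no randomisation strata. Section 4 says that confounders such as cognitive state are included, and Table 2 lists Glasgow score and agitation among them, but Section 2.6 describes no method that uses them.

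**The concern.** VAS is the patient's own rating. FLACC and PAINAD, as the protocol names and assigns them, are used where self-report is not relied on: young children and people with cognitive impairment. A shared 0–10 range does not make a 5 on one the same as a 5 on another. With one variable and one unadjusted two-group rule, the default is a comparison across all three. A pooled mean difference then has no clear unit, and a Mann–Whitney test ranks a FLACC score against a VAS score.

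Two things are at stake. One is how the pain result can be read; pain is among the stated aims at the end of the Introduction. The other is precision: any difference in score level between instruments goes into the error term, although the instrument depends on age and cognition, which are fixed before the puncture.

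The assignment rules also conflict. Section 3.1 leaves ages 5 to 7 without a scale and gives VAS above 7, whereas Table 2 gives FLACC to paediatric patients without an age limit. Until this is settled, the instrument, and so the stratum, is undefined for some children.

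**Working it through.** **No plan figure to reproduce.** The protocol states no pain SD, effect or sample size. Its venous sample size (Section 2.4) rests on number of attempts. I use it only for the number of patients available: 95 before the allowance for losses, 95/2 = 47.5, taken as 47 evaluable per arm. Randomising 57 per arm and losing 20% would leave 57 × 0.8 = 45.6, which is close.

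**Assumed inputs (none is in the documents).** Within-instrument SD σ = 2.0 (2.5 as a check). True difference δ = 1 point, the same on every instrument. VAS/FLACC/PAINAD shares from 85/10/5 to 50/25/25. FLACC mean above the VAS mean by 0, 1 or 2 points, and PAINAD mean below it by the same amount.

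**Formulas.**

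- Between-instrument variance: B = Σ w(m − m̄)², with share w, instrument mean m and overall mean m̄.
- Pooled SD = √(σ² + B); variance ratio = 1 + B/σ².
- Power = Φ(δ / (SD·√(2/n)) − 1.96), two-sided 5%, n = 47 per arm.
- SD of the chance shift in the arm difference from uneven instrument mix = √(2B/n).

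**Analysed by instrument, σ = 2.** √(2/47) = 0.2063; 1/(2 × 0.2063) = 2.424; Φ(2.424 − 1.96) = 68%.

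**Pooled, σ = 2.**

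| Shares | Offset | B | Variance ratio | Power | SD of chance shift |
|---|---|---|---|---|---|
| any | 0 | 0 | 1.00 | 68% | 0 |
| 85/10/5 | 1 | 0.15 | 1.04 | 66% | 0.08 |
| 85/10/5 | 2 | 0.59 | 1.15 | 62% | 0.16 |
| 70/15/15 | 1 | 0.30 | 1.08 | 65% | 0.11 |
| 70/15/15 | 2 | 1.20 | 1.30 | 57% | 0.23 |
| 50/25/25 | 1 | 0.50 | 1.13 | 63% | 0.15 |
| 50/25/25 | 2 | 2.00 | 1.50 | 51% | 0.29 |

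The last row in full: B = 0.25 × 4 + 0.25 × 4 = 2; SD = √6 = 2.45; 1/(2.45 × 0.2063) = 1.98; Φ(1.98 − 1.96) = 51%.

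**Check with σ = 2.5.** Power is 49% by instrument and falls to 39% pooled in the most extreme case (variance ratio 1 + 2/6.25 = 1.32).

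**Type I error.** In 20,000 simulated null trials per setting (94 patients, 2-point offsets, scores confined to 0–10), the pooled t-test rejected in 4.9% (50/25/25) and 5.1% (70/15/15).

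**The case against.** The strongest reply is that pooling is never stated. Table 2 is a list of recorded variables, Section 2.6 is a general rule that does not mention pain, and a fuller plan that is not shown might separate the instruments. This stands in part: pooling follows by default and is not an outright commitment. But Section 2.6 does fix a test, and that test does not suit an outcome measured on three instruments.

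Second, a reader might infer that case mix biases the pain result. The documents do not support that. With 1:1 randomisation the expected shift is zero and type I error holds; only chance imbalance remains, as with any baseline factor left out of an unadjusted test.

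Third, the size rests wholly on assumptions, which is true. Nor can the share of children serve as the FLACC share. Visit counts in Section 2.1 and prevalences in the Introduction give 5,000 × 0.37 / (5,000 × 0.37 + 42,000 × p) = 15.5% at p = 0.24 and 30.6% at p = 0.10, if visits reflect eligibility. That counts all children, while Section 3.1 gives FLACC only below age 5.

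Fourth, pain is not in the hypothesis or main objective and sizes neither part of the trial, and Section 4 presents the several scales as a deliberate way to include children and cognitively impaired patients. That limits the weight of the point. Using several scales is reasonable; the issue is how their scores are compared.

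**Conclusion.** The point holds as one of interpretation and efficiency, not validity. As written, the plan compares non-equivalent pain scores together by default, so the pooled difference is hard to read. Precision is lost only if score levels differ between instruments. Under the assumptions shown, the variance ratio runs from 1.00 to 1.50 and power for a 1-point difference at σ = 2 from 68% (no loss) to about 51%. Chance imbalance moves the arm difference by an SD of at most about 0.3 points. These figures concern the venous part and illustrate a range; they do not estimate what will happen in this trial.

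The disagreement between Section 3.1 and Table 2 over which children get which scale needs no assumption: it is visible in the text.

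**What to change.** 1. Reconcile Section 3.1 with Table 2 so that every patient, including children aged 5 to 7 and those over 7, has exactly one instrument fixed before the puncture. Which scale applies is for the investigators to decide.
2. Add the instrument used as a separate field on the data form; Table 2 lists none.
3. State in Section 2.6 that pain is compared stratified by instrument, with the van Elteren test as the main analysis, because it ranks scores only within an instrument. A linear model with instrument as a factor would remove differences in mean level but still assumes one common effect in points across scales that are not equivalent, so it is better kept as supporting.
4. Show the treatment difference within each instrument. Small strata will be imprecise: a 5% share of 94 patients is 94 × 0.05 = 4.7 people.

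The cost is a few sentences and one form field, with no additional patients.
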